### Sample size

The aim of the HEART study is to evaluate whether the use of the HEART score streamlines the further management of chest pain patients, in particular whether it can identify low-risk patients who can be discharged sooner than usual. However, these benefits become only relevant if the use of the HEART score does not lead to an increase in adverse cardiac events. Our sample size calculation is therefore based on demonstrating that proportion of patients with MACE is not inferior to the proportion observed with usual care. The proportion MACE expected during usual care is 17%. The non-inferiority margin is based on clinical judgement and available literature as 3%, thus accepting an upper limit of the 95% confidence interval (CI) during the intervention period of 20%. With 10 hospitals, inclusion of 60 patients per hospital per month, a between-hospital variation in incidence of 16 to 18%, a one-sided alpha of 5% and a power of 80%, 6600 patients with chest pain should be included in total. Taken into account our inclusion rates of previous validation studies and with special attention and encouragement for inclusion, we expect a realistic inclusion rate of 60 patients per hospital per month.

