				**Total**
**Number of patients**	N = 880 [12]	N = 2388 [13]	N = 2906 [14]	N = 6174
**Design**	Retrospective	Prospective	Prospective	
**Countries**	The Netherlands	The Netherlands	9 countries in the Asia-Pacific region	
**Participating hospitals**	4	10	14	
**Inclusion period**	Jan ‘06 – Mar ‘06	Oct ‘08 –Nov ‘09	Nov ‘07 – Dec ‘10	
**Type of patients**	Patients presenting with chest pain at the ED	Patients presenting with chest pain at the ED	Patients presenting with chest pain at the ED	
**MACE definition**	AMI, revascularisation, all cause death	AMI, revascularisation, stenosis managed conservatively, all cause death	AMI, revascularisation, death unless clearly non-cardiac	
**Duration of follow-up**	6 weeks	6 weeks	4 weeks	

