### Statistical analyses

The 6-week cumulative incidence of MACE in both the intervention and usual care period will be analysed at the patient level using a generalised linear mixed model (GLMM) [21]. Risk differences with corresponding 95% CIs will be estimated from this model. No baseline differences in prognostic factors between patients included in both periods are expected, but in case these do occur, covariates will be added to the GLMM model to adjust for these baseline differences. Differences in health-related quality of life at baseline, 2 weeks and at 3 months will also be assessed, separately for the different questionnaires. Costs per patient will be calculated according to Dutch guidelines for pharmaco-economic analyses [22], and costs of drugs prescribed will be based on Dutch formulary cost-prices.

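### The written non-inferiority limit is a 20% ceiling on HEART-period incidence, which does not match the plan's own 3-point margin against observed usual care

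*Protocol article*

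**What the plan says.** The Sample size section gives the aim as "demonstrating that proportion of patients with MACE is not inferior to the proportion observed with usual care", so the comparator is what the trial observes under usual care. It then states a planning rate ("The proportion MACE expected during usual care is 17"%) and a margin ("The non-inferiority margin is based on clinical judgement and available literature as 3"%). The same sentence turns the margin into a limit: "thus accepting an upper limit of the 95% confidence interval (CI) during the intervention period of 20"%. The calculation closes with "a one-sided alpha of 5% and a power of 80%, 6600 patients with chest pain should be included in total".

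The Statistical analyses section specifies a generalised linear mixed model and adds: "Risk differences with corresponding 95% CIs will be estimated from this model". It does not say what that interval is to be compared with.

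**The concern.** The 20% limit is the only confidence limit in the article that is tied to non-inferiority, and it sits on the wrong quantity. It bounds the incidence in one period, whereas the margin concerns the difference between two periods. A ceiling fixed in advance takes no account of the usual-care rate actually observed, of the sampling error in that rate, or of the stepped-wedge comparison.

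If usual-care MACE is below 17%, the ceiling leaves room for an excess larger than 3 points. If it is above 17%, the ceiling can fail a strategy that does no harm. This is the primary safety conclusion, and an analysis plan that copied the sentence as written would carry the mismatch forward.

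**Working it through.** **Inputs.** From Study design and Sample size: 10 hospitals, 11 months, 60 patients per hospital per month, one hospital switching each month after a first usual-care month, expected rate 17%, margin 3 points, one-sided alpha 5%, power 80%. Assumption: the between-hospital range of 16 to 18% is read as mean ± 2 SD, so SD τ = 0.005. Results for τ from 0 to 0.01 are also given.

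**1. The plan's own total.** 10 × 11 × 60 = 6600. The layout has 55 usual-care and 55 HEART hospital-months, so 55 × 60 = 3300 patients in each condition.

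**2. Power of a difference test.** Hussey-Hughes variance with fixed period effects and a random hospital effect:

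Var = I·s²(s² + Tτ²) / [(I·U − W)s² + (U² + I·T·U − T·W − I·V)τ²]

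Here I = 10, T = 11, U = 55, W = V = 385 and s² = 0.17 × 0.83 / 60 = 0.002352. The denominator coefficients are 550 − 385 = 165 and 3025 + 6050 − 4235 − 3850 = 990. With τ = 0.005, Var = 0.0001496 and SE = 0.01223.

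- One-sided 5%: Φ(0.03/0.01223 − 1.645) = Φ(0.807) = 79.0% (80.7% at τ = 0, 75.1% at τ = 0.01).
- Upper limit of a two-sided 95% CI (one-sided 2.5%): Φ(2.452 − 1.960) = Φ(0.492) = 68.9%. Reaching 80% would take about 80 per cell, or 80 × 110 = 8800 patients.

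The stated 80% is thus reproduced to within about a point by a difference test at one-sided 5%.

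**3. Pass probability of the literal ceiling.** SE_H = √[p(1−p)/3300 + τ²/10]. The ceiling passes with probability Φ((0.20 − p)/SE_H − 1.96). At p = 0.17, SE_H = 0.00673 and the result is Φ(4.459 − 1.96) = 99.4%. That is far from 80%, so 6600 was not derived from the ceiling.

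**4. The two rules compared** (τ = 0.005):

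| Usual care / HEART | Ceiling, two-sided 95% CI | Ceiling, one-sided 5% | Difference test, two-sided 95% CI | Difference test, one-sided 5% |
|---|---|---|---|---|
| 17% / 17% | 99% | >99% | 69% | 79% |
| 16% / 19% (at margin) | 30% | 41% | 2.5% | 5% |
| 15.2% / 18.2% (at margin) | 74% | 83% | 2.5% | 5% |
| 18% / 18% | 83% | 90% | 67% | 78% |
| 19.5% / 19.5% | 11% | 17% | 64% | 75% |

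Example: at 18.2%, SE_H = 0.00690 and Φ(0.018/0.00690 − 1.96) = Φ(0.649) = 74%. For τ from 0 to 0.01 this figure runs from 76% to 68%, and the 16%/19% figure from 31% to 26%.

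**5. Where 15.2% comes from.** It is a scenario. Solving n = 1.96²·p(1−p)/h² from the half-widths h of Table 2's pooled intervals gives about 2000, 3120 and 1045 patients in the three strata, or shares of 0.324, 0.506 and 0.170. Then 0.324 × 1.6 + 0.506 × 12.5 + 0.170 × 49.4 = 15.2%. The same shares with the Dutch prospective rates give 0.324 × 1.7 + 0.506 × 16.6 + 0.170 × 50.1 = 17.5%.

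**The case against.** The strongest reply is that the 20% is shorthand in a sample-size paragraph. The aim names the observed usual-care proportion, the margin is stated before the 20%, the 17% is called an expectation, and the analysis section plans risk differences. The sample size also works only on the difference scale. All of this stands, and it makes a difference test the probable intent. A reader might infer that the trial has abandoned a limit on the difference, or that the randomised comparison would play no part in the verdict. The documents do not support either inference.

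A reader might also infer that the ceiling gives the wrong answer whenever usual care departs from 17%. It does not. With both rates at 18% it passes 83% of the time, which is the right verdict, and at exactly 17% the two rules already differ (99% against 69%).

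Nor do the documents show that 17% is wrong. The Dutch prospective study in Table 2 counted a broader endpoint ("AMI, revascularisation, stenosis managed conservatively, all cause death") than this trial does, which makes a lower rate plausible. But the 15.2% rests on a pooled column whose high-risk rate (49.4%) lies below all three of its components (65.2%, 50.1% and 50.0%), and which includes a study with 4-week follow-up.

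Finally, a condensed article may leave the formal decision rule to a fuller document. That would answer a complaint that the rule is absent. It does not answer this one, because the article writes out a limit and puts it on a quantity that disagrees with its own aim.

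**Conclusion.** The point holds as a misplaced decision limit. The plan states a 3-point margin against observed usual care, then expresses it as a ceiling on HEART-period incidence that agrees with neither the aim, the planned effect measure nor the sample size. If the ceiling were applied as written, the chance of declaring non-inferiority exactly at the margin would be about 30% with usual care one point below the planning rate, against the 5% that the stated alpha allows. It would be about 74% in the 15.2% scenario. With both rates at 19.5% it would pass about 11% of the time.

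These figures are conditional on the literal reading, a normal approximation, 3300 HEART-period patients and the assumed τ of 0.005. Varying τ from 0 to 0.01 does not change the conclusion.

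The same sentence carries a second mismatch: it names a 95% confidence interval, while the sample size uses one-sided 5%, which corresponds to the limit of a two-sided 90% interval.

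**What to change.** Replace the clause on the 20% limit with a statement along these lines: non-inferiority is concluded if the upper confidence limit of the risk difference (HEART minus usual care) from the mixed model is below 3 percentage points. Keep 20% only as an illustration of what the margin means at an expected 17%.

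Name the confidence level in the same edit. A one-sided 95% limit (the upper limit of a two-sided 90% interval) fits the stated alpha and keeps about 79% power at 6600. If the upper limit of a two-sided 95% interval is wanted, power at 6600 should be restated as about 69%, or the total raised to about 8800 to reach 80%.

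Under the first choice the cost is one sentence, with no change to sample size, data collection or model. It should be settled before outcome data are compared between periods.

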### Cost-effectiveness analysis

A cost-effectiveness analysis will be performed from a societal perspective, for a 3-month and a life-time time horizon. The 3-month time horizon corresponds to the actual follow-up period and will consider the observed differences in costs and quality of life. A GLMM will be used to assess cost-effectiveness, accounting for the randomisation of clusters instead of patients. Uncertainty will be addressed through the GLMM model which will be extended with cluster and patient-level covariates if baseline characteristics are imbalanced. The life-time horizon will be applied to account for long-term costs and effects of the observed MACE. Here, the observed risks of MACE, as well as the direct treatment cost and productivity losses estimated using the friction cost approach, will serve as input for a Markov decision-analytic model [23]. If necessary, additional evidence on long-term costs and effects of adverse events will be obtained from the literature. Monte Carlo simulation will be applied to simulate the course of hypothetical patients through the model, and to estimate the number of quality-adjusted life years and costs of both strategies. Costs will be discounted with 4% per annum, and effects with 1.5% per annum, according to Dutch guidelines. The incremental cost-effectiveness ratio and the net monetary benefit (for various willingness to pay thresholds) will be estimated for the HEART score compared with usual care. Uncertainty will be assessed with probabilistic sensitivity analysis [24], and results will be presented in incremental cost-effectiveness planes and cost-effectiveness acceptability curves.

### Regulation statement

This study will be conducted according to the principles of the current version of the declaration of Helsinki and in accordance with the Dutch law on Medical Research Involving Human Subjects Act (WMO).

### Ethics committee approval

The study was approved by the Institutional Review Board (medical ethical committee of the University Medical Center Utrecht, the Netherlands), and subsequently by the Boards of the participating hospitals.

## Discussion

Clinical prediction rules, like any other health care intervention, need proper evaluation before wide-spread use in clinical practice. Two key steps in this evaluation include external validation and impact assessment. External validation studies can reveal several problematic issues associated with the use of a clinical prediction rule [25-27]. Firstly, the rule has been developed on a dataset that was too small in relation to the number of variables that have been considered. This increases the risk that particularities of the dataset will be modeled rather than robust relationships. The consequence is that the performance of the model will decrease when applied to new patients (external validation). This is known as over-fitting. Secondly, the rule has been derived in a population which does not match the population where clinicians would like to use the rule. Here, your prediction model may be developed statistically sound, but applied to a new population the performance may decrease meaningfully. However, even after proper development and good performance in validation studies, often clinical prediction rules are hardly or incorrectly used in daily practice, because of difficulties in application or because physicians are not convinced of its usefulness in clinical practice. This is especially the case when the outcome used in the rule has no direct relevance for clinical practice. For all these reasons, it is of vital importance to study the impact of a clinical prediction rule when applied in real-life practice. Increasingly, stepped wedge designs are applied to measure the impact of clinical decision rules in clinical practice [28]. The stepped wedge design combines elements of both the cluster randomised trial and the before-after design (see Figure 1). The stepped wedge design has several features that make this design attractive for such impact studies. These characteristics are outlined in Table 3. We chose the stepped wedge design as an informative, efficient and valid design to examine whether expected improvements in patient outcomes, use of health care resources, and costs can be achieved when implementing a health care intervention on a large scale.

**Table 3 T3:** Overview of key characteristics of the stepped wedge design

(i) →	Stepped wedge design has features of cluster randomisation, i.e. during a specific time period only type of intervention (usual care or HEART score) is administered
a. →	This reduces the risk of contamination
b. →	The effect of clustering needs to be taken into account in the statistical analysis
(ii) →	Stepped wedge design has features of a one direction cross-over trial, i.e. each hospital contributes data from both usual care and HEART score in a fixed order.
a. →	Allows for comparison of results within hospitals which may be less confounded by differences in case mix than between hospitals
b. →	The fixed order from usual care to HEART score further reduces the risk of contamination as the HEART score is relatively simple to calculate.
c. →	Due to the cross-over, each hospital will provide data about the (problems in) implementation of the HEART score
(iii) →	Switch from usual care to HEART score in hospitals is evenly and randomly distributed over calendar time
a. →	This reduces the impact of potential changes over time in other factors than the intervention
b. →	It facilitates the close monitoring and logistic of all activities surrounding the switch
(iv) →	Gradual implementation of new strategy is carried out, thereby providing data about the process itself.

## Conclusion

It is of importance to generate valid evidence that the use of the HEART score compared to usual care is safe and leads to fewer admissions and diagnostic procedures in real-life clinical practice. Using the stepped wedge design, we can also monitor the process of implementation of a clinical support tool at the ED across hospitals that vary in size and population. Patient inclusion has started July 1st of 2013.
